### Interventions

2.9

#### Source and distribution of research objects

2.9.1

The patients will be randomly divided into the experimental and control groups (both n = 126). Eighty-four cases will be obtained in the Second Affiliated Hospital of Heilongjiang University of Traditional Chinese Medicine, Changchun University of Chinese Medicine, and China Rehabilitation Research Center.

#### Treatment

2.9.2

The experimental group will undergo acupuncture at the appropriate neck acupoints as follows:

Nape cluster acupuncture treatment of the oral stage will employ the bilateral Fengchi, Gongxue, swallowing 2, Jiachengjiang, Xiaguan, Yingxiang, Lianquan, Waijinjin, Waiyuye, and Tongzhong acupoints.

Nape cluster acupuncture treatment of the pharynx stage will employ the bilateral Fengchi, GongXue, swallowing 2, Tiyan, Zhiqiang, swallowing 1, Phonation, Lianquan, Zhifanliu, Waijinjin, Waiyuye and Tongzhong acupoints.

The acupoints and acupuncture methods are described below. The Fengchi acupoint is at the same level as the Fengfu point, at the depression between the trapezius and sternocleidomastoid muscles. The needle tip will be slightly tilted downward and inserted 2 cm deep into the Adam's apple. The GongXue point is 2 cm below the FengChi point and flushes with the lower lip. The needle will be inserted 2 cm deep into the opposite lip. The swallowing 2 point is located at the flat chin lip groove and posterior edge of the sternocleidomastoid muscle. Here, the needle tip will be directly inserted approximately 1.5 to 2 cm into the opposite side and retained for 30 minutes. The JiaChengJiang point is on the face, 1 inch adjacent to the Chengjiang point. The XiaGuan point is ventral to the tragus and mandibular condyle at the depression formed by the zygomatic arch and mandibular notch. The Yingxiang point is located half an inch from the alar margin midpoint in the nasolabial groove.

The Lianquan point is located at the hyoid depression above the Adam's apple, with the needle being inserted 3 cm into the tongue base, twisted for 10 to 15 s, and then removed. The Waijinjin and Waiyuye acupoints are 1 cm on each side of the Lianquan point, with the needle being inserted 2 to 3 cm into the tongue base, twisted for 10 s, and then removed. The Tongzhong point (Juquan point) is at the middle of the tongue, with the needle being inserted 0.1 cm into the tongue and then removed. For the Fengchi, Gongxue, Jiachengjiang, Xiaguan, and Yingxiang acupoints, the needles will be retained in the insertion point for 30 min.

The Tiyan point, the needle will be directly inserted forward and downward at 1 to 1.5 cm at the depression in front of the mastoid and the lower earlobe edge. The Zhiqiang point is located between the hyoid bone and thyroid cartilage notch, with the needle being directly inserted approximately 0.3 to 0.5 cm, twisted for 10 to 15 s, and then removed. The swallowing 1 point is located at 0.5 cm adjacent to the midline between the hyoid bone and laryngeal node, with the needle being inserted approximately 0.5 cm laterally along the skin, twisted for 15 s, and then removed. The phonation point is located 0.5 cm below the midline of the Adam's apple; specifically, between the thyroid and cricoid cartilages. The needle will be inserted approximately 0.5 cm along the skin, twisted for 10 to 15 s, and then removed. The Zhifanliu point is located 1 cm behind the pronunciation point, the posterior edge of the cricoid cartilage, and the cricopharyngeal muscle. Regarding operation, the needle will be obliquely pierced 0.5 cm inward along the skin and removed after twisting for 10 to 15 s.

The control group will undergo swallowing function rehabilitation training. A tongue muscle rehabilitation device will be used to perform tongue muscle activities in the directions of front and back, up and down, left and right, oblique down, etc. Moreover, the patients will perform training involving mouth opening and closing, chewing, frowning, smiling, cheek puffing, and the Mendelssohn technique to promote swallowing. The lingual and soft palates will be stimulated using ice and acid.

##### Dysphagia in the oral stage

2.9.2.1

1.Jaw, face, and cheek exercisesThe participant's mouth will be maximally opened, held for 5 s, relaxed for 3 s, and repeated 5 times. Moreover, the participants will close the lips, puff their cheeks, hold for 5 s, relax for 3 s, and repeat 5 times. Air will be rapidly moved around the left and right cheeks by puffing the cheeks 10 times. The participants will bare their teeth for 5 s for five sessions with 3-s relaxation intervals. Moreover, the participants will purse their lips for 5 s, relax for 3 s, and repeat the procedure five times. Finally, they will perform chewing movements ten times with 20-s intervals in between.2.Lip exercisesThe participants will clench their teeth and pronounce Yi, hold for 5 s, and relax for 3 s for a total of five sessions. Moreover, the participants will purse their lips and pronounce Wu, hold for 5 s, and relax for 3 s for a total of five sessions. Next, the participants will alternately pronounce Yi and Wu for 3 s each and repeat the pronunciation twice in each session. The participants will complete three sessions and relax for 5 s. With tongue depressors on both lips, the participants will forcefully pull out the tongue depressor, resist with closed lips, hold for 5 s, and relax for 2 s, with the procedure being repeated five times. Regarding the blowing exercise, the participants will blow five times and breathe evenly for two cycles after each expiration, with a 20-s interval break.3.Tongue exercisesThe participants will remove the tongue as far as possible out of the mouth, hold for 5 s, and retract and relax for 3 s, with this procedure being repeated ten times. Moreover, the participants will lift the tongue to the back of the front teeth, hold for 5 s, and relax for 3 s, with this procedure being repeated ten times. Furthermore, in each session, the participants will extend the tongue tip to the left and right lip angle for 2 s, with this procedure being repeated three times. The participants completed three sessions and relaxed for 5 s. Moreover, the participants will lick their lips with the tongue tip ten times with 20-s break intervals.4.Velopharyngeal closure exercisesAn ice cotton stick will be used to stimulate the palatopharyngeal arch; simultaneously, the participants will pronounce “a” thrice, relax for 3 s, and repeat the procedure five times with 10-s break intervals.5.Respiratory exercisesThe participant will breathe deeply by the nose while lifting the shoulders, and subsequently breathe out and relax. Each session will involve two respiratory cycles. The participants will complete three sessions with even breathing and a 5-s rest after each session. A 10-s break will be taken.6.Mendelsohn's techniqueHere, the patients will be instructed to swallow empty air. The therapist will push the patient's throat using the hand to promote swallowing and the procedure will be repeated five times, with a 10-s break.

##### Dysphagia in the pharyngeal stage

2.9.2.2

1.Tongue trainingThe participant will extend the tongue from the mouth as much as possible, maintain it there for 5 s, and then retract and relax for 3 s, with the procedure being repeated 10 times. Moreover, they will open the mouth, lift the tongue to the back of the front teeth, maintain it there for 5 s, relax for 3 s, with the procedure being repeated 10 times. Additionally, in each session, the participants will extend the tongue tip to the left and then the right lip corner thrice for 2 s. Further, the participants will complete three sessions with 5-second relaxation breaks. Finally, the participants will lick the lips with the tongue tip and repeat 10 times, with a 10-s break.2.Velopharyngeal closure training:To stimulate the velopharyngeal arch with an ice cotton swab will be used, and participant will simultaneously be instructed make a sound three times, relax for 3 s, repeat five times, and hold a break for 10 s.3.Breathing training:The patients will be instructed to deeply inhale through the nose while lifting the shoulders; subsequently, they will shrink the mouth, exhale, and relax. Each session will be comprised of two breathing cycles. The participants will complete three sessions while breathing and resting for 5 s after each session. A 10-s break will be provided in between.4.Mendelssohn manipulationThe patient will swallow empty air, with the therapist pushing the patient's throat using the hands to promote swallowing. The procedure will be repeated five times with a 10-s break.5.Direct feeding training.We will adopt empty, interactive, and side swallowing methods using viscous and uniform food for feeding training.

### Outcome assessment

2.10

#### Evaluation indexes

2.10.1

The primary outcome indicators will be the SSA and VFSS, while the secondary outcome indicators will be the sEMG signal analysis and MBI. The common evaluation index will be the SS-QOL while the follow-up indicators will be the SS-QOL and SSA.

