### Study design

2.2

This will be a multicenter, randomized controlled study conducted at the Second Affiliated Hospital of Heilongjiang University of Traditional Chinese Medicine, Changchun University of Traditional Chinese Medicine, and China Rehabilitation Research Center from December 1, 2018, to December 31, 2021. Patients with post-stroke dysphagia who meet the inclusion criteria will be divided into the experimental and control groups using a central randomization system. The experimental and control groups will receive acupuncture treatment and conventional rehabilitation training, respectively. The primary results will be obtained using the standardized swallowing assessment (SSA), videofluoroscopic swallowing study (VFSS), and fMRI. The secondary observation indicators will include surface electromyography (sEMG) analysis and modified Barthel index (MBI). The follow-up indicators include stroke-specific quality of life scale (SS-QOL) and the SSA. Measurements will be obtained before treatment, as well as 1 week, 2 weeks, and 1 month after treatment. fMRI will be only performed in the subject unit. Forty-two participants will undergo pre- and post-treatment fMRI assessment to analyze the central regulatory mechanism underlying swallowing function remodeling in the rehabilitation program of TCM. Figure 1 and Table 1 present the technology roadmap and clinical observation flow charts, respectively.

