**Figure 1 F1:**
[figure not shown]
Present the technology roadmap.

**Table 1 T1:** Clinical observation flow charts.

Research stage	Selection period	Treatment period		Follow-up period
Evaluation times	First time	Second	Third time	Fourth
Evaluation time point	1 and 0 days before treatment	1 week after intervention	2 weeks after intervention	1 month after the end of the intervention
Inclusion criteria	•			
Exclusion criteria	•			
Informed consent form	•			
Online random grouping	•			
General assessment				
General information	•			
Current medical history/allergic history	•			
Past history/complications	•			
Evaluation of the curative effect index				
VFSS	•		•	
SSA	•	•	•	•
Surface electromyography signal	•	•	•	
Improved Barthel index	•	•	•	
SS-QOL				•
Security assessment				
Life indication	•	•	•	•
Other assessments				
Adverse reactions/events		•	•	
Recurrence situation				•
Treatment compliance			•	

SSA = standardized swallowing assessment, SS-QOL = stroke-specific quality of life scale, VFSS = videofluoroscopic swallowing examination.

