#### Evaluation time

2.10.2

Measurements will be obtained before the intervention, 1 week after intervention, and 2 weeks after intervention. The follow-up time point will be 1 month after the end of the intervention.

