### Sample size calculation

2.16

Referring to Liu Zhishun's “clinical study on acupuncture treatment of chronic moderate and severe dysphagia in stroke,” the effective rate of traditional rehabilitation is 80%, the estimated effective rate is 93.3%. According to the preset parameters, the effectiveness of the two groups were calculated with PASS 8.0 software, and 97 samples were needed for each group. At the same time, abscission and elimination were considered. The abscission rate was 30% and each group needed 126 samples. Therefore, 252 subjects were expected to be included in this study.

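### SS-QOL is scheduled only at the 1-month follow-up, so there is no baseline value for a change score or as a covariate, and the text and Table 1 do not agree on its role

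*Protocol article*

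**What the plan says.** Four places in the protocol article bear on when SS-QOL is measured.

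- **Section 2.2 (Study design)** lists it only for follow-up: "The follow-up indicators include stroke-specific quality of life scale (SS-QOL) and the SSA".
- **Table 1** has one mark in the SS-QOL row, in the follow-up column headed "1 month after the end of the intervention". The selection-period, week 1 and week 2 cells are empty.
- **Section 2.10.1 (Evaluation indexes)** names the scale twice in one sentence: "The common evaluation index will be the SS-QOL while the follow-up indicators will be the SS-QOL and SSA". It is not among the primary outcomes (SSA and VFSS) or the secondary outcomes (sEMG and modified Barthel index).
- **Section 2.10.2 (Evaluation time)** gives the times without naming an instrument: "Measurements will be obtained before the intervention, 1 week after intervention, and 2 weeks after intervention". A follow-up one month after treatment comes next.

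**The concern.** Section 2.10.1 reads as if SS-QOL serves both as a general index and as a follow-up measure, and section 2.10.2 speaks of pre-treatment measurement in general terms. Table 1 gives SS-QOL no pre-treatment assessment. A site working from the text and a site working from the table could therefore collect different data.

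If Table 1 governs, each patient contributes a single post-treatment score. Within-patient change cannot be computed, and the covariate likely to be most closely related to the 1-month score is missing. A statistical analysis plan written later cannot repair this, because a baseline that was not collected cannot be recovered. At stake are the precision and interpretability of the only quality-of-life measure in the trial.

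**Working it through.** **Is the single mark real?** Set out by instrument, Table 1 gives:

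| Measure | Baseline | Week 1 | Week 2 | 1 month | Total |
|---|---|---|---|---|---|
| SSA | yes | yes | yes | yes | 4 |
| sEMG | yes | yes | yes | no | 3 |
| "Improved Barthel index" | yes | yes | yes | no | 3 |
| VFSS | yes | no | yes | no | 2 |
| SS-QOL | no | no | no | yes | 1 |

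The SS-QOL mark lies in the same column as recurrence, which is a follow-up item by nature, so it is not a displaced baseline mark. Section 2.2 agrees with it. SSA, the other follow-up indicator, is marked at all four evaluations, so the missing baseline is particular to SS-QOL.

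**What a baseline would be worth.** The plan states no SS-QOL standard deviation, effect or correlation, so there is no figure of its own to reproduce. Let ρ be the correlation between baseline and 1-month SS-QOL (an assumption). Relative to comparing 1-month scores with no covariate, the variance of the arm difference is:

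- baseline as covariate: 1 − ρ²
- change score: 2(1 − ρ)

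| ρ (assumed) | Covariate: 1 − ρ² | Cut in variance | Equivalent extra patients: 1/(1 − ρ²) − 1 | Change score: 2(1 − ρ) |
|---|---|---|---|---|
| 0.3 | 0.91 | 9% | 10% | 1.40 |
| 0.5 | 0.75 | 25% | 33% | 1.00 |
| 0.7 | 0.51 | 49% | 96% | 0.60 |

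The covariate analysis is better than the change score at each of these values. At ρ = 0.3 the change score is less precise than using no baseline at all.

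**The same in detectable differences.** Inputs are 97 evaluable patients per arm (section 2.16), with two-sided 5% significance and 80% power (both assumed, as the article states neither). The detectable difference in SD units is (1.960 + 0.842) × √(1 − ρ²) × √(2/97):

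- no covariate: 2.802 × 0.1436 = 0.40 SD
- ρ = 0.3: 0.40 × √0.91 = 0.38 SD
- ρ = 0.5: 0.40 × √0.75 = 0.35 SD
- ρ = 0.7: 0.40 × √0.51 = 0.29 SD

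With all 126 per arm, the corresponding values are 0.35, 0.34, 0.31 and 0.25 SD.

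**Gain over the covariates already available.** Baseline SSA and Barthel index can be used as the schedule stands, so the figures above are upper bounds on what baseline SS-QOL would add. As an illustration, suppose those two explain 25% of the variance and adding baseline SS-QOL raises this to 49%. Residual variance then falls from 0.75 to 0.51, and 1 − 0.51/0.75 = 32%, rather than 49%. If baseline SS-QOL raised the explained variance no further than that 25%, the extra gain would be nil.

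**The case against.** The strongest reply is that a follow-up-only quality-of-life measure is a legitimate design in a randomised trial. Randomisation makes the 1-month comparison valid without a baseline, a change score is not needed to compare arms, and no primary or secondary conclusion rests on SS-QOL. All of this stands, and it limits the priority of the point.

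Three stronger readings are tempting, and the document supports none of them.

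- *That the arm comparison cannot be adjusted at all, or that imbalance and selective loss cannot be examined.* SSA, VFSS, sEMG and Barthel index are all measured before treatment. They can serve as covariates, and SSA and Barthel index at baseline, week 1 and week 2 allow patients lost before one month to be compared with completers and can inform imputation. Only adjustment for, and comparison on, baseline SS-QOL itself are lost.
- *That up to 30% of patients will lack an SS-QOL score.* Section 2.16 says "The abscission rate was 30% and each group needed 126 samples", but the sentence before it shows that the allowance covers elimination as well as drop-out, and nothing ties it to the 1-month visit.
- *That the baseline was left out by design.* Table 1 is not complete: it has no fMRI row, although section 2.2 plans fMRI before and after treatment. The SS-QOL row could be incomplete too, and section 2.10.1 can be read that way. This does not remove the point. Section 2.2 supports the table, and if a baseline was intended, the table has to say so.

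**Conclusion.** The point holds as a minor one. Table 1 and section 2.2 place SS-QOL only at follow-up, while sections 2.10.1 and 2.10.2 leave room for earlier measurement, so the passages need reconciling. As scheduled, SS-QOL change cannot be computed and the 1-month comparison cannot use baseline SS-QOL as a covariate. The loss is mainly one of precision. Bias remains a concern only through selective loss before one month, as it would for any outcome at that visit.

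The size rests wholly on the assumed correlation: a 9% to 49% cut in variance for ρ from 0.3 to 0.7, measured against no covariate at all, and less against adjustment for SSA and Barthel index. The primary and secondary outcomes and the sample size are unaffected.

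**What to change.** 1. In Table 1, add an SS-QOL mark at the first evaluation, in the day before treatment or on the day itself. Treatment is not blinded and the scale is about quality of life, so it is best completed before the allocation is known.
2. Bring sections 2.2, 2.10.1 and 2.10.2 into line with Table 1, and state in one place what role SS-QOL has and when it is measured.
3. Compare arms on the 1-month score with baseline SS-QOL as a covariate, in preference to a change score.
4. For patients already enrolled without a baseline SS-QOL, adjust for baseline SSA and Barthel index. If enrolment is too advanced for the addition to be useful, describe SS-QOL as a single post-treatment comparison adjusted for those two measures, and correct section 2.10.1 accordingly.

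The cost is a few minutes of patient time at a visit that already takes place. Patients already enrolled will have no baseline value, and the document does not show how many they are.

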#### Evaluation time

2.10.2

Measurements will be obtained before the intervention, 1 week after intervention, and 2 weeks after intervention. The follow-up time point will be 1 month after the end of the intervention.

### Ethical considerations

2.11

After the research plan is formulated by the project undertaking unit and approved by experts, it will be reported to the ethics committee of the project undertaking unit for approval. Each participating unit will report to the ethics committee to review its feasibility. Before study enrollment, the patients will be informed regarding the research background, purpose, benefits, and risks. The patients will be enrolled after providing informed consent. The adherence of the subjects was improved by scientific informed consent, active health education, humanistic care and long-term follow-up plan,.

### Quality control

2.12

To ensure the research quality and data validity, we will conduct unified and standardized training for the study researchers, formulate clinical research SOPs, and ensure that the clinical research consistently follows the operating procedures. Regular monitoring will be used to ensure the study's authenticity and reliability.

### Data management

2.13

To establish a database, all data will be double-entered using computer software to compile a data entry program. The data manager will ensure the completeness and integrity of the data in the case report form report entered into the computer. The data will be blindly reviewed; moreover, after correct confirmation, the data will be locked by the main researchers and statistical analysts.

### Randomization and allocation concealment

2.14

The main researchers of each unit will be assigned different user names and passwords to establish a central random system and data collection system. Before treatment, the patient information will be entered into the central random system; moreover, the patient will be screened according to the inclusion and exclusion criteria. Patients who meet the criteria will be randomly divided into the control and experimental groups.

### Blinding

2.15

In this study, due to the specificity of clinical acupuncture research, it is difficult to implement blind method. But it can be assessed by people who are not involved. We plan to assign specialized doctors from rehab centers as reviewers, and they will not be told how the subjects are grouped.

### Sample size calculation

2.16

Referring to Liu Zhishun's “clinical study on acupuncture treatment of chronic moderate and severe dysphagia in stroke,” the effective rate of traditional rehabilitation is 80%, the estimated effective rate is 93.3%. According to the preset parameters, the effectiveness of the two groups were calculated with PASS 8.0 software, and 97 samples were needed for each group. At the same time, abscission and elimination were considered. The abscission rate was 30% and each group needed 126 samples. Therefore, 252 subjects were expected to be included in this study.

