### Inclusive criteria

2.4

The inclusion criteria will be as follows: clinical diagnosis of first-episode unilateral cerebral hemisphere infarction or cerebral hemorrhage, with confirmation using CT or MRI; meeting the diagnostic criteria for dysphagia; showing abnormal expressions of the oral and pharynx stages upon VFSS evaluation; having stroke and dysphagia duration within 3 months; being conscious with stable vital signs and a mini-mental state examination score of ≥ 21; age 45 to 75 years; and having provided informed consent.

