## Discussion

3

Dysphagia refers to swallowing dysfunction.^[11]^ Clinical patients are commonly in the oral, pharyngeal, or both stages. The mouth stage is the chewing food process to form a bolus, with the tongue moving the bolus back and forth before entering the pharynx. Dysfunction involves weakness of the facial muscles, including the chewing, labial, and tongue muscles, which impedes food bolus formation and smooth delivery to the pharynx. The pharyngeal stage refers to the process of the food bolus entering the oropharynx into the esophagus. This stage involves abnormal pharyngeal muscle and laryngeal function, which often causes aspiration, pharynx retention, and hoarseness.^[12]^

The SSA is divided into three parts: clinical examination, observation of patients swallowing 5 mL of water, and observation of patients swallowing 60 mL of water. It has a total score of 46, with the lowest possible score being 17. A higher cumulative score of each item indicates worse swallowing function. Some studies have reported that SSA is more feasible and suitable for evaluating dysphagia.^[13]^ The SSA includes 10 items divided into four levels: independent, less dependent, moderately dependent, and completely dependent. The VFSS allows dynamic assessment of the swallowing function of the mouth, pharynx, and upper esophagus using TV fluoroscopy. The VFSS is considered the “gold standard” for evaluating swallowing function. It is widely used for the comprehensive evaluation of the patients’ oral, pharyngeal, and esophageal swallowing conditions.^[14]^ The sEMG allows evaluation of the physiological process of swallowing. It is a simple and reliable screening that allows preliminary identification of dysphagia and has advantages of accuracy, rapidity, and non-invasiveness.^[15]^ fMRI is a safe, non-invasive, and non-radiation imaging method with high temporal and spatial resolution. Anatomical and functional images can be simultaneously obtained in a single imaging session.^[16]^

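### The sample size rests on an undefined effective rate that is not a listed outcome, so power is not established for any named primary outcome, and the 80% control rate is not justified for this population

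*Protocol article*

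**What the plan says.** Section 2.16 takes its planning rates with reference to a study titled "clinical study on acupuncture treatment of chronic moderate and severe dysphagia in stroke" and states that "the effective rate of traditional rehabilitation is 80%, the estimated effective rate is 93.3" (both percentages). It does not say what makes a patient effective, on which instrument, or when. Significance level, sidedness and power are not given either: "According to the preset parameters, the effectiveness of the two groups were calculated with PASS 8.0 software". The result is 97 per group, raised to 126 for a 30% loss, 252 in all.

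Section 2.10.1 names the outcomes: "The primary outcome indicators will be the SSA and VFSS, while the secondary outcome indicators will be the sEMG signal analysis and MBI". Section 2.2 has a longer list of primaries: "The primary results will be obtained using the standardized swallowing assessment (SSA), videofluoroscopic swallowing study (VFSS), and fMRI". Follow-up uses SS-QOL and SSA. Table 1 schedules these measures (apart from fMRI) and has no row for an effective rate. The Discussion describes the SSA as a score: "It has a total score of 46, with the lowest possible score being 17". No standard deviation or target difference is given for the SSA, and no rate or cut-off for VFSS.

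On population, section 2.4 requires "having stroke and dysphagia duration within 3 months" and sets no minimum severity.

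**The concern.** A sample-size section should show what the trial can detect on the outcome it will test. Here the calculation is for a binary responder outcome, while the outcome sections name a score and an imaging assessment with no responder rule. Both sections are in the document and they do not meet.

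Two things are at stake. First, nobody can tell from section 2.16 what difference in SSA or VFSS the trial can detect. Second, if an effective rate later appears as the main result because it matches the calculation, nothing in this document fixes its cut-off, its instrument or its time point.

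The reference adds a separate doubt. By its title it concerns chronic moderate and severe dysphagia, and this trial takes patients within 3 months of onset. An 80% control rate may or may not carry over, and the article does not argue that it does.

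**Working it through.** **Inputs from the document.** Rates 0.80 and 0.933, 97 per group before loss, 30% loss, 126 per group (section 2.16); 1:1 allocation (section 2.9.1); SSA range 17 to 46 (Discussion). **Assumed, because not stated:** two-sided 5%, 80% power.

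**1. Reproducing 97.** Arcsine formula for two proportions:

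- h = 2·asin(√0.933) − 2·asin(√0.80) = 2.618 − 2.214 = 0.404
- n = 2(1.960 + 0.842)² / h² = 96.3, rounded up to **97**, the stated figure.

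The unpooled normal formula gives 99 and the pooled one 102. At 90% power, two-sided, the formulas give 129 to 150, which does not fit. The stated size is therefore a comparison of two responder proportions.

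**2. Matching it to the outcomes.**

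| Place | What is named |
|---|---|
| 2.16 | Effective rate, undefined |
| 2.2 | Primary: SSA, VFSS, fMRI; secondary: sEMG, MBI; follow-up: SS-QOL, SSA |
| 2.10.1 | Primary: SSA, VFSS; secondary: sEMG, MBI; follow-up: SS-QOL, SSA |
| Table 1 | VFSS, SSA, sEMG, Barthel index, SS-QOL |

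The endpoint of the first row appears in none of the others.

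**3. What the size offers for a score.** For one two-sided 5% test with 80% power, the detectable standardised difference is (1.960 + 0.842)·√(2/n):

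- n = 126: 0.35 SD
- n = 97: 0.40 SD
- n = 88 (126 × 0.70 = 88.2): 0.42 SD

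If alpha were split equally between SSA and VFSS (2.5% each, an assumption), these become 0.39 SD at 126 and 0.46 SD at 88. The document has no SSA standard deviation, so none of these can be turned into points.

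**4. Dependence on the control rate, if the effective rate is kept.** Arcsine power at 97 per group = Φ(h·√(97/2) − 1.960). What happens as the control rate moves depends on what is held constant. The planned odds ratio is (0.933/0.067)/(0.80/0.20) = 3.48; the planned gap is 93.3 − 80 = 13.3 points.

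| Control rate | Power, odds ratio 3.48 held | Power, 13.3-point gap held |
|---|---|---|
| 70% | not tabulated | 60% |
| 75% | 88% | 68% |
| 80% | 80% | 80% |
| 85% | 69% | 96% |
| 90% | 52% | not possible (103.3%) |

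The two columns run in opposite directions. The control rate matters under both assumptions, but neither the size nor the sign of the effect on power is settled by the document.

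**The case against.** The strongest reply is that no shortage of power has been shown, and that is right. Suppose *effective* were a cut-point on a roughly normal score with equal spread in both groups (an assumption). Then 80% against 93.3% would correspond to a shift of 1.50 − 0.84 = 0.66 SD, well above the 0.42 SD detectable at 88 per group; power there would be about 99%. A reader might infer from section 2.16 that the trial has no power for SSA or VFSS, or is too small. The document does not support that; power is undocumented, not absent.

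A reader might also infer that early natural recovery raises the control rate and so erodes power. The document does not state such recovery, and the table above shows that a higher control rate lowers power only if the odds ratio is held. With the gap held, power rises.

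The population point has limits. *Chronic* is known only from the title of the cited study. The sentence structure also leaves open whether the 93.3% comes from that study or is the authors' own estimate. What stands is that the mismatch is visible and unexplained.

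On a cut-off chosen late, section 2.17 gives the analysis plan to a third party, section 2.13 provides blind data review and locking, and section 2.15 keeps assessors unaware of group. These reduce the risk. They do not remove it, because section 2.17 does not place the analysis plan before the data. A responder definition could properly sit in a fuller document, but that would not explain why the endpoint used for sizing is missing from the article's own outcome list.

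Finally, 88 per group is the pessimistic count. The full analysis set in section 2.17 takes all treated patients and carries observations forward, so up to 126 per group may be analysed.

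**Conclusion.** The point holds as a conflict between section 2.16 and sections 2.2, 2.10.1 and Table 1. The 97 per group is sound arithmetic for 80% against 93.3%, given the assumed two-sided 5% and 80% power, but it belongs to an outcome the trial does not list. Power for SSA and VFSS is therefore not established.

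For scale, a single score outcome tested at 5% has a detectable difference between 0.35 SD (126 per group) and 0.42 SD (88 per group), larger if alpha is shared. If the responder outcome is what is meant, its power at 97 per group lies anywhere from 52% to 96% over the control rates and two effect assumptions examined. The 80% control rate needs a justification for patients within 3 months of onset. It has not been shown to be wrong.

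This should be corrected, and text alone can do it.

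**What to change.** Keep 252 patients. Before any outcome data are seen, take one of two routes.

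**(a) Keep the effective rate.** Define it by a fixed cut-off on SSA or VFSS at a fixed time point, list it in section 2.10.1 as the primary outcome, justify the 80% control rate for this population, say where the 93.3% comes from, and state power over a range of control rates (for example 75% to 90%) under a declared effect assumption, constant odds ratio or constant difference.

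**(b) Size for the outcome that is tested.** Name that outcome and its time point, and restate section 2.16 for it. For the SSA score this would be 0.35 SD at 126 per group and 0.42 SD at 88, for one two-sided 5% test with 80% power, converted to points with a standard deviation that the sponsor supplies and sources. If SSA and VFSS both remain primary, say how alpha is handled and give the larger detectable difference that follows, with a corresponding statement for VFSS.

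Under either route, state alpha, sidedness and power in section 2.16 and make the primary list the same in sections 2.2 and 2.10.1.

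The cost is redrafting. No patients or visits are added. The drawback is that the stated power may look less favourable than the present text suggests.
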